# Ensuring a Successful Transition From Cytology to Human Papillomavirus–Based Primary Cervical Cancer Screening in Canada by Investigating the Psychosocial Correlates of Women’s Intentions: Protocol for an Observational Study

**DOI:** 10.2196/38917

**Published:** 2022-06-16

**Keywords:** human papillomavirus, HPV-based primary screening, cervical cancer, cervical cancer screening, cancer prevention, knowledge, attitudes and beliefs, preferences, HPV test acceptability, HPV self-sampling, Pap testing, cytology, mobile phone

## Abstract

**Background:**

The human papillomavirus (HPV) test has emerged as a significant improvement over cytology for primary cervical cancer screening. In Canada, provinces and territories are moving toward implementing HPV testing in cervical cancer screening programs. Although an abundance of research exists on the benefits of HPV-based screening, there is a dearth of research examining women’s understanding of HPV testing. In other countries, failure to adequately address women’s concerns about changes has disrupted the implementation of HPV-based screening.

**Objective:**

The aims of the multipart study described in this paper are to develop psychometrically valid measures of cervical cancer screening–related knowledge, attitudes, and beliefs; to examine the feasibility of a questionnaire examining psychosocial factors related to HPV-based screening; and to investigate psychosocial correlates of women’s intentions to participate in HPV-based screening.

**Methods:**

We conducted a web-based survey (study 1) of Canadian women to assess the acceptability and feasibility of a questionnaire, including the validation of scales examining cervical cancer knowledge, HPV testing knowledge, HPV testing attitudes and beliefs, and HPV test self-sampling attitudes and beliefs. Preferences for cervical cancer screening were assessed using the best-worst scaling methodology. A second web-based survey (study 2) will be administered to a national sample of Canadian women between June 2022 and July 2022 using the validated scales. Differences in the knowledge, attitudes, beliefs, and preferences of women who are currently either underscreened or adequately screened for cervical cancer will be examined through bivariate analyses. Multinomial logistic regression will be used to estimate the associations between psychosocial and sociodemographic factors and intentions to undergo HPV-based screening.

**Results:**

Between October 2021 and November 2021, a total of 1230 participants completed the questionnaire in study 1, and 1027 (83.49%) responses were retained after data cleaning methods were applied. Feasibility was comparable with similar population-based surveys in terms of survey length, participant attrition, and the number of participants excluded after data cleaning. As of May 2022, analysis of study 1 is ongoing, and results are expected to be published in the summer of 2022. Data collection is expected to begin for study 2 in the summer of 2022. Results are expected to be published between late 2022 and early 2023.

**Conclusions:**

Findings will provide direction for Canadian public health authorities to align guidelines to address women’s concerns and optimize the acceptability and uptake of HPV-based primary screening. Validated scales can be used by other researchers to improve and standardize the measurement of psychosocial factors affecting HPV test acceptability. Study results will be disseminated through peer-reviewed journal articles; conference presentations; and direct communication with researchers, clinicians, policy makers, media, and specialty organizations.

**International Registered Report Identifier (IRRID):**

DERR1-10.2196/38917

## Introduction

### Background

Cervical cancer is the fourth most common cancer in women and presents a significant risk to all people with a cervix [1-3]. In 2018, an estimated 570,000 women were newly diagnosed with cervical cancer worldwide, with 311,000 deaths from the disease [4]. In Canada, >1300 women are diagnosed with and >400 women die from cervical cancer each year [5]. Cytology testing using the Papanicolaou smear, commonly referred to as the Pap test, allows for the detection and subsequent treatment of precancerous lesions that may lead to cervical cancer. Canadian women have been widely screened for cervical cancer using the Pap test for >50 years [6]. There are guidelines in each province and territory that currently recommend screening every 1 to 3 years, starting at the age of 21 or 25 years [7], and most Canadian jurisdictions have organized screening programs [8].

Cervical cancer is caused by persistent infection with high-risk human papillomavirus (HPV) types [9]. The HPV test, which detects high-risk HPV DNA in cervical cells, has emerged as a significant improvement over cytology for cervical cancer screening. Compared with cytology-based screening, HPV-based screening has been shown to offer 60% to 70% higher protection against the development of cervical cancer [10,11]. The HPV test shows improved sensitivity, and negative test results have high negative predictive value, thus providing greater reassurance against cervical lesion development [12]. Furthermore, this allows for increased intervals between cervical screenings and reduced testing costs [12]. HPV testing also introduces the possibility for vaginal self-sampling by the patient. This is not possible with cytology, which requires cervical cell collection by a health care provider, a process that can be uncomfortable or invasive [13,14]. Meta-analyses have shown that self-sampling has similar test accuracy when compared with health care provider–administered sampling [15] and could increase uptake among those who are underscreened when provided as a screening option [15,16].

Therefore, currently, HPV testing is considered the preferred method of screening by the World Health Organization [17] and is recommended by multiple specialty organizations worldwide (eg, United States Preventive Services Task Force [18], European Society of Gynaecologic Oncology, and European Federation of Colposcopy [19]). Several countries have implemented HPV-based organized screening programs (eg, Australia, the United Kingdom, and the Netherlands), including the use of self-sampling as a collection option [20,21]. However, program implementations have encountered challenges. For example, in Australia, before the introduction of HPV testing, a web-based petition against the proposed changes gained widespread support. In an analysis of comments on the petition, Australian women felt that the policy *devalued or threatened women’s health* and represented a government cost-cutting measure and that increased screening intervals and later age of screening initiation would prevent early detection of cervical abnormalities [22]. Similarly, in Wales, increase in screening intervals associated with the shift to HPV-based screening has been met with public backlash, with >1.2 million signatures on a web-based petition against the change at the time of writing [23]. Although these guidelines are grounded in evidence, a disconnect has been observed between women’s and public health authorities’ views on cervical cancer screening changes. These health authorities failed to effectively and proactively communicate why changes were warranted, why screening intervals may change, and what HPV test results indicate [22-26].

### Screening Landscape in Canada

In Canada, provinces and territories are in different planning phases for HPV-based cervical cancer screening programs [7,27], and the nationwide introduction of HPV-based primary screening is a key priority of the recent Canadian Partnership Against Cancer (CPAC) Action Plan for the Elimination of Cervical Cancer [5]. Although cytology-based screening is well established in Canada, screening coverage has failed to reach the CPAC target of including ≥80% of women [28]. This suggests that innovative approaches are needed to reach those women who are underscreened (ie, longer than 3 years since their previous Pap test or never screened). Approximately 40% of women in Canada diagnosed with cervical cancer report either never having had a Pap test or not having had one in >3 years [29]. Underscreened women are often members of ethnic, linguistic, gender, and sexual minorities or have lower socioeconomic status [30-33]. In Canada, only 65% of recent female immigrants reported having a Pap test in the previous 3 years, and 26% of non-English or French speakers reported never having a Pap test [29]. In a study of cancer screening registries in Ontario, transgender patients were significantly less likely than cisgender patients to be screened for cervical cancer (56% vs 72%) [32], reflective of barriers faced by transgender and other gender-diverse people in seeking cervical cancer screening [2]. A study by Decker et al [34] comparing screening rates and outcomes between First Nations women and all other women in Manitoba suggested lower screening rates among First Nations women aged ≥40 years and significantly higher rates of cervical lesions and cancers in First Nations women overall. Targeted solutions must consider these factors. For underscreened women, the introduction of HPV self-sampling could be important for ensuring that cervical cancer screening is more accessible and acceptable [13-15,35,36]. A meta-analysis of 37 studies by Nelson et al [37] found that women who used and indicated acceptability of self-sampling for future screening did so because of its convenience, privacy, and ease of use. However, identified barriers include women’s lack of confidence in their ability to correctly collect the specimen, lack of confidence in the test result, and discomfort with the procedure [37,38].

The concerns of adequately screened women (ie, <3 years since their previous Pap test) must also be addressed. Clear and open dialogue with these women is needed to prevent confusion and provide reassurance that the switch to HPV-based screening is evidence-based and represents an improvement over cytology-based screening. Currently, there is a dearth of research examining Canadian women’s perceptions and understanding of HPV-based screening and potential changes to screening guidelines. To avoid problems that may arise in Canada as program implementations advance, efforts should be made to understand and address the concerns of women.

### Measuring Knowledge, Attitudes, and Beliefs About Cervical Cancer Screening

From both theoretical and practical perspectives, knowledge is a determinant of engagement in protective health behaviors [24,39,40]. In a systematic review of psychosocial factors associated with intentions and acceptability of HPV testing, knowledge was associated with greater acceptability of screening using the HPV test [24]. In Canada, poor cervical cancer screening knowledge has been identified as a key barrier to screening in populations such as immigrant women and ethnic minority communities [41-43]. In a recent systematic review, specific attitudes and beliefs about HPV testing have been identified as both barriers to and facilitators of HPV test acceptability [24]. For example, high perceived benefits of the HPV test were associated with greater HPV test acceptability, whereas negative emotions (eg, shame associated with testing for a sexually transmitted infection) related to HPV testing were associated with lower HPV test acceptability. Importantly, these findings and many additional attitudes and beliefs (eg, high perceived susceptibility to cervical cancer, negative perceived emotional reaction to HPV test results, and high perceived severity of HPV infection) have not been studied and confirmed in Canada-wide samples.

Several measures exist for cervical cancer knowledge [44-47], a subscale has been developed for measuring knowledge of HPV testing [48], and 2 measures of HPV testing and self-sampling attitudes and beliefs have been developed [49,50]. However, existing measures have shown insufficient psychometric testing or suboptimal psychometric properties. In addition, in a fast-moving field, many measures are not up-to-date with evidence from the literature on cervical cancer and HPV testing or do not include other important factors associated with HPV test acceptability (eg, negative emotions related to HPV testing [24]). As women’s perceptions of cervical cancer and HPV testing are multifaceted, comprehensive and valid measurement tools are crucial for identifying attitudes, beliefs, and knowledge gaps that could be barriers to the acceptance and uptake of HPV-based screening.

### Measuring Preferences Regarding Cervical Cancer Screening

Preferences refer to a distinct form of attitude that provides information about the relative value and ranking an individual assigns to certain options over others. Measuring preferences is important in the context of cervical cancer screening, as multiple approaches (eg, varying screening intervals and use of self-sampling) are being considered for implementation [5]. Understanding Canadian women’s preferences can provide insight into the acceptability of different screening options and illuminate any potential disconnect between women and public health regarding the implementation of HPV-based screening programs. In particular, by examining women’s preferences for screening intervals and age of screening initiation, 2 major points of contention observed in other program implementations [22,51,52], public health can optimize communications to address concerns and ensure acceptability of HPV-based screening guidelines [24]. Furthermore, examining the preferences of underscreened women and adequately screened women separately can help to inform targeted communications for these groups.

### This Study

The proposed study will use a multistep approach to examine women’s knowledge, attitudes, beliefs, and preferences toward HPV testing and self-sampling. A preparatory study (study 1) was focused on the development and psychometric validation of scales measuring cervical cancer screening–related knowledge, attitudes, and beliefs. In addition, given the challenges of investigating women’s views toward a screening approach that has not yet been implemented, this study examined the feasibility and structure of a survey that examines these factors in Canadian women. Results of study 1 will yield validated scales to administer to a large sample of Canadian women (study 2) to estimate the associations between psychosocial factors and women’s intentions to participate in HPV-based screening programs. Furthermore, study 2 will survey and compare differences in psychosocial factors and HPV test intentions among adequately screened women and underscreened women, providing timely data to address emerging challenges in both groups.

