##### Item Selection

To evaluate potentially relevant items together and guide their selection, a large pool of items (n=781) was created, and a questionnaire structure was drafted (Figure 1) with 4 potential scales: cervical cancer knowledge, HPV testing knowledge, HPV testing attitudes and beliefs, and HPV self-sampling knowledge. This large item pool included items from the reviewed scales and new items generated based on the results of a recent mixed methods synthesis of psychosocial factors affecting HPV test acceptability [24] and a systematic review of emotional responses to testing positive for HPV [25]. Items related to sociodemographics and health behaviors were also included.

All 781 items were compiled into an Excel (Microsoft Corporation) spreadsheet to be reviewed by the research team. A flowchart of the item sources is shown in Figure 2. Each item was reviewed individually over several research team meetings, marked as *retained* or *rejected*, and categorized into an appropriate section of the questionnaire (Figure 1). For instance, the item “The HPV test is safe” was categorized as part of *attitudes and beliefs about HPV testing* instead of *knowledge about HPV testing* because this item captures a belief that women may agree or disagree with, which may impact their intentions to engage in cervical cancer screening with the HPV test. Within each of the questionnaire sections, items were further mapped onto constructs from the HBM (eg, “if the HPV test showed I have HPV, it would be serious” in perceived seriousness) and TPB (eg, “my friends’ opinion about getting the HPV test would be important to me” in social cues) to ensure comprehensive coverage of these frameworks.

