**Figure 2 figure2:**
[figure not shown]
Flowchart of item sources.

At this stage, the focus was on the item’s underlying construct and not its wording. Reasons for rejecting items included the following: (1) duplicate of a factor already retained, (2) not applicable to Canadian context (eg, “There are resources in my community for low and no cost cervical cancer screenings” as Canada has a universal health care system [45]), (3) infrequent and isolated factor (eg, “I worry that tube contents may spoil or spill during transportation to doctor” [63]), and (4) not applicable to our project’s quantitative and survey methodology (eg, open-ended items such as “There are many warning signs and symptoms of cervical cancer. Please name as many as you can think of” [44]).

In total, of 781 items that were reviewed, 137 (17.5%) items were retained. Of these 137 items, 85 items were categorized for scale development: 14 for cervical cancer knowledge, 14 for HPV testing knowledge, 44 for attitudes and beliefs about HPV testing, and 13 for attitudes and beliefs about HPV self-sampling. These 85 items were reviewed and revised separately for clarity, consistency, and grade-8 reading level to account for different language and literacy levels. In addition, certain cervical cancer knowledge and HPV testing knowledge items were revised to achieve a balance of *true* and *false* items (ie, made negative or affirming by adding words such as *not*).

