##### Data Analysis—Objective 1: Scale Validation

To evaluate dimensionality, we will conduct EFA and CFA separately for cervical cancer knowledge, HPV testing knowledge, and HPV testing and self-sampling attitudes and beliefs items. The final data set will be split randomly into 2 equal samples, and one sample will be used to conduct EFA and the other sample will be used to validate the factor structure using CFA. To select the optimal number of factors, we will use the parallel analysis approach and the syntax developed by O’Connor [85]. For items within each factor, we will use item response theory modeling; for binary data (knowledge items), we will use the 2-parameter logistic regression model that accounts for item difficulty and discriminant capacity; and for ordinal data (attitudes and beliefs items), we will use the graded response model that accounts for discriminant capacity and probability of selecting a certain Likert scale score (eg, strongly agree). Concurrently, we will examine how well each item measures the latent trait by plotting the item information against the latent construct ability. We aim to retain items that cover a wide range of difficulty and have high discriminant capacity and information value. To estimate the CFA model fit, we will use the fit indices and cutoff criteria recommended by Hooper et al [86]: (1) relative (normed) chi-square test (*χ*^2^/_df_=2 to 5) by Wheaton et al [87], (2) standardized root mean square residual (<0.8), (3) root mean square error approximation (<0.06), (4) comparative fit index (≥0.95), and (5) Tucker-Lewis index (≥0.95). To evaluate internal consistency for items loading onto each factor, Cronbach *α* will be calculated.

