#### Study Design

A cross-sectional web-based survey will be administered in summer of 2022 to a nationally representative sample of Canadian women, aged 21 to 70 years, in English and French. The study population and inclusion criteria will be the same as those in study 1. Oversampling will be used to ensure that half of the sample is adequately screened and the other half is underscreened. Additional quotas will be used for the following factors: age, household income, and rural or urban residence (considering low cervical screening rates in rural Canada [7]) based on census data from Statistics Canada. Data collection will be conducted by Dynata, following the same procedure as that in study 2.

The questionnaire will follow the same structure and include the same sections as the survey detailed in study 1. Of the knowledge, attitudes, and beliefs items used for scale development in study 1, only those items retained after extensive psychometric analyses will be used in the study 2 questionnaire as part of the resulting shorter, validated scales. In addition, 2 previously validated measures, the extended HPV General Knowledge and HPV Vaccine Knowledge scales, will be added [69], given the relevance of HPV and HPV vaccination in cervical cancer. The measurement of the outcome variables (intentions to screen using the HPV test and self-sampling) is informed by PAPM [81], a categorical, stage-based model of health decision-making. As a binary, *yes or no* outcome limits accuracy, using a multistage model provides a more precise, nuanced understanding of women’s decision-making process that acknowledges the unique barriers associated with movement between each stage toward engaging with the behavior [90].

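### The stated scale-validation analyses cannot show that the two knowledge scales are distinct, and they relate no score to an outside variable, before the scales are called validated and used as separate predictors in study 2

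*Protocol article*

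**What the plan says.** The claim is strong and is made in several places. This Study says: "Results of study 1 will yield validated scales to administer to a large sample of Canadian women (study 2) to estimate the associations". The Conclusions of the abstract add: "Validated scales can be used by other researchers to improve and standardize the measurement of psychosocial factors affecting HPV test acceptability". Principal Findings expects the scales to set the standard for measuring these constructs.

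The analyses behind the claim are in Data Analysis—Objective 1: Scale Validation. On dimensionality: "we will conduct EFA and CFA separately for cervical cancer knowledge, HPV testing knowledge, and HPV testing and self-sampling attitudes and beliefs items". On sampling: "The final data set will be split randomly into 2 equal samples", one half for EFA and the other for CFA. Item response models and five fit indices follow. On reliability: "To evaluate internal consistency for items loading onto each factor, Cronbach" alpha is to be computed. The item pools, in Item Selection, are "14 for cervical cancer knowledge, 14 for HPV testing knowledge, 44 for attitudes and beliefs about HPV testing" and 13 for self-sampling attitudes.

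Other validity work came first. In Item Selection, "items were further mapped onto constructs from the HBM" and from the Theory of Planned Behavior. Collaborators reviewed the content (Questionnaire Revisions and Translation), and seven women gave cognitive interviews (Phase 1B).

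In study 2, Study Design states: "2 previously validated measures, the extended HPV General Knowledge and HPV Vaccine Knowledge scales, will be added". Data Analysis enters predictors that pass a bivariate screen at P<.10 together in a multinomial model and reports an odds ratio for each.

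**The concern.** Each statistical step listed works inside one item set. A factor model fitted to the cervical cancer knowledge items alone, and another fitted to the HPV testing knowledge items alone, may both fit well whether the two sets reflect two constructs or one. The allocation of items to sets was a team judgement (Item Selection), and factoring each set alone cannot test it.

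Nor does any listed step relate a score to something outside the scale. Study 1 collected suitable variables: post-secondary education, HPV vaccination and intention stage.

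This matters because the second objective of study 2 is multivariable. Separate odds ratios for two knowledge scales have separate meanings only if the scales measure different things. With the two added scales there may be four HPV-related or cervical cancer knowledge scores in one model. The article also offers the scales to other researchers as validated, and they would take that to cover more than internal structure and content.

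**Working it through.** **1. The plan's own figures.** Study 1 size: 2 × 500 / 0.82 = 1219.5, so 1220, as stated. Study 2: 10 × 15 / 0.25 = 600; 600 / 0.40 = 1500 per screening group; 3000 / 0.82 = 3659, against the stated approximate 3650. All reproduce to rounding. The point concerns which evidence is planned, not arithmetic.

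**2. Evidence set against the claim.**

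| Type of evidence | In the article? | Where |
|---|---|---|
| Content | Yes | Item Selection; Questionnaire Revisions and Translation |
| Response process | Yes, 7 interviews | Phase 1B |
| Structure within a set | Yes | Scale Validation |
| Reliability | Yes, alpha per factor | Scale Validation |
| Distinctness of the two knowledge sets | None stated | – |
| Distinctness of the two attitude sets | Unclear: joint or separate factoring | Scale Validation; Sample Size |
| Relation to an outside variable before use | None stated | – |

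The wording in Scale Validation could mean that testing and self-sampling attitudes are factored together. Study 1 Sample Size, which works from the 13 self-sampling items alone, leans towards separately. Only the knowledge sets are clearly separate.

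**3. Consequence if the knowledge scales overlap (illustration).** The documents give no inter-scale correlations, so r is assumed. For four predictors with equal pairwise correlation r, VIF = (1 + 2r) / [(1 − r)(1 + 3r)]. The interval widens by about √VIF, and the 600-observation contrast carries the information of about 600 / VIF. In a multinomial model this is an approximation.

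| Assumed r | VIF | Interval widening | 600 / VIF |
|---|---|---|---|
| 0.6 | 2.2 / 1.12 = 1.96 | 1.40 | 305 |
| 0.7 | 2.4 / 0.93 = 2.58 | 1.61 | 232 |
| 0.8 | 2.6 / 0.68 = 3.82 | 1.96 | 157 |

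With only two overlapping scales, VIF = 1 / (1 − r²): 1.33 at r = 0.5, 1.96 at 0.7 and 3.60 at 0.85.

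**4. Can study 1 supply the missing evidence?** 1027 responses were retained, about 513 per half. On the Fisher z scale the half-width is 1.96 / √(n − 3), which is 0.061 for n = 1027. An observed correlation of 0.85 would have a 95% interval of about 0.82 to 0.87 in one half and 0.83 to 0.87 in the full sample. This is a guide only, since a latent correlation has its own standard error. For a known-groups comparison with two equal groups of 513 (assumed), 80% power at two-sided 0.05 needs d = (1.96 + 0.84) × √(2/513) = 0.175. Unequal groups would need a somewhat larger d.

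**The case against.** The strongest reply is that this is an omission from a condensed article. No analysis plan is shown, study 1 analysis was still under way, and inter-scale correlations or collinearity checks are often left to a fuller document. That has weight, and further checks may exist there. But Scale Validation is not a sketch: it names the parallel-analysis syntax, both item response models and five fit cutoffs. It also states a method, separate factoring of the knowledge sets, that cannot test distinctness.

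Second, the plan meets the standard it sets in Literature Search, where earlier scales are faulted for lacking full factor analysis or reliability testing. True, but that standard does not cover reading scales as separate predictors.

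Third, study 2 itself relates scores to screening group and intention stage. That also stands, so the complaint about outside variables is partly one of timing: the label is applied first.

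A reader might infer several stronger things that the documents do not support:

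- That validation rests on internal structure alone. The theory mapping, expert review and interviews rule this out.
- That all item sets are factored apart. The attitudes wording is ambiguous.
- That a high alpha could simply reflect agreement style across a long item pool. Alpha is computed per factor, and study 1 Sample Size assumes about 4 items per factor. With alpha = kr / [1 + (k − 1)r], 4 items at a mean inter-item r of 0.10 give 0.4 / 1.3 = 0.31. Knowledge items were also balanced between true and false.
- That study 2 is shown to be too small. The correlations are assumed, scales must first pass the P<.10 screen, and collinearity is not invalidity: two distinct scales correlated at 0.7 have the same VIF, so proving distinctness would not narrow the intervals.

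**Conclusion.** The point holds in limited form. The statistical validation stated in the article covers internal structure and reliability, on top of real content and response-process work. It cannot show that cervical cancer knowledge and HPV testing knowledge are two constructs, and it ties no score to an outside variable before the scales are called validated and enter study 2 with two further knowledge scales.

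Nothing in the documents shows that the scales do overlap or are invalid. The size of any harm is unknown. The 1.4- to 2.0-fold widening of intervals rests wholly on assumed pairwise correlations of 0.6 to 0.8 among four scales that all enter the model. It illustrates imprecision, and a joint CFA would not remove it. The CFA would settle whether the separate odds ratios have separate meanings. This is an inexpensive improvement rather than a flaw that undermines either study, and as of May 2022 study 2 data collection had not begun.

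**What to change.** Add to Data Analysis—Objective 1: Scale Validation, using data already collected:

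1. In the CFA half, fit one joint model of the two knowledge item sets. Do the same for the two attitude sets if they are not already factored together. Compare merged with separate factors, report latent correlations with intervals, and merge scales that fail a distinctness criterion written down before the fit, such as a stated upper limit for the latent correlation.
2. State in advance a few known-groups or convergent tests, with expected direction: knowledge by post-secondary education and by HPV vaccination; attitudes by intention stage.

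In study 2 Data Analysis, report the correlations among the four knowledge scales before they enter the same model.

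If these steps are not taken, describe the scales as structurally validated in the abstract, This Study and Principal Findings.

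The cost is a little more analysis, with no new items or participants. The downside is that a scale may have to be merged or described more cautiously.
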